#### Thickness of the fat and muscle layer of the face

The BodyMetrix 2000 device, a linear ultrasound with a depth of 60mm, will be used to assess the thickness of the facial muscles. The method is safe, emits no radiation, and is non-invasive. During the assessment, the participant will remain in a comfortable position, and a conducting gel will be applied to the skin over the masseter. The device will be slid from the origin to the insertion of the muscle, aiming to obtain precise information. The ultrasonographic images generated will be subsequently analyzed using the BodyView software, for thickness of tissue layers in the facial region.

### Interventions

#### Group 1 –Local photobiomodulation

The treatment will be administered over 2 weeks, totaling 4 sessions [2 sessions per week] with an average duration of 6 minutes per session.

Participants will be positioned in a clinical chair for the application of photobiomodulation. The interventions will be conducted by a trained professional. Group 1 will receive photobiomodulation using the Therapy EC–DMC device, with a red wavelength of 660 nm and power of 100 mW, properly calibrated, delivering 6J per point [60 seconds] at 2 points in the masseter muscle region, 1 point in the left temporal muscle,1 point in the right temporal muscle, 1 point in the left trapezius muscle in the cervical region, 1 point in the right trapezius muscle. The total application time will be 4 minutes per session.

At the time of application, only the participant receiving the treatment, the researcher responsible for the treatment, and the guardian will be present. Everyone will wear specific goggles for eye protection. The equipment’s tip will be disinfected with 70% alcohol and covered with disposable transparent plastic [PVC] to prevent cross-contamination, while the facial area to be irradiated will be cleaned with a 0.2% Chlorhexidine solution. During the applications, the participant will remain seated, with the Frankfurt plane parallel to the ground. Energy penetration will be analyzed at one of the points on the masseter muscle.

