**Fig 1 pone.0309073.g001:**
[figure not shown]
The SPIRIT schedule of enrolment, interventions, and assessments.

**Table 1 pone.0309073.t001:** Dosimetric parameters for photobiomodulation application.

PARAMETERS	RED LASER [Local]	INFRARED LASER [Transcutaneous Systemic]
Wavelength [nm]	660	808
Mode	Contínuo	Contínuo
Power [mW]	100	100
Aperture Diameter [cm]	0,354 [beam diameter with spacer]	0,354 cm
Beam Area [cm^2^]	0,0984 [with spacer]	0,0984 cm^2^
Exposure Time [s]	60 per point	600 s
Fluence [J/cm^2^]	61	-
Energy [J]	6 per point	60 J
Number of irradiated points	6	Systemic
Application Technique	Contact	Contact
Number of sessions	4	4
Treatment Frequency	2 times per week	2 times per week
Total Irradiated Energy [J]	144 J	240 J

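### The local laser session is stated as both 6 minutes and 4 minutes; the listed points and Table 1 need 6 minutes, and 4 minutes would deliver two thirds of the tabulated energy

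*Protocol article*

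**What the plan says.** The conflict lies within one subsection of the Protocol article, Interventions, Group 1 – Local photobiomodulation.

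- The schedule is "totaling 4 sessions [2 sessions per week" and so on over two weeks, "with an average duration of 6 minutes per session".
- The device is set "with a red wavelength of 660 nm and power of 100 mW".
- The points are given as "delivering 6J per point [60 seconds] at 2 points in the masseter muscle region", then "1 point in the left temporal muscle,1 point in the right temporal muscle", then "1 point in the left trapezius muscle in the cervical region, 1 point in the right trapezius muscle".
- The same paragraph closes with "The total application time will be 4 minutes per session".

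Table 1 gives for the local laser: power 100 mW, 60 s per point, 6 J per point, a beam area of 0.0984 cm², a fluence of 61 J/cm², 4 sessions and a total of 144 J. Its row "Number of irradiated points" reads 6. The Group 3 subsection gives the local placebo arm the same procedures as Group 1, with no light emitted.

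**The concern.** Two times are given for the same session, and the shorter one is labelled as the total application time. The laser-on time implied by the point list is already 6 minutes, so a 4-minute total cannot hold it at 60 s per point.

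This is an operating instruction for an active arm, not background text. Operators who follow different sentences would deliver different energies under the same group label. The primary outcome is orofacial pain, and the Expected results section looks for a difference between local and vascular treatment. The exposure behind the local arm should therefore have one value. Group 3 takes its procedure from Group 1, so the sham session inherits the same uncertainty about its length.

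**Working it through.** **Inputs.** From the Group 1 text and Table 1: power 100 mW = 0.1 W; 60 s per point; 4 sessions. From the Group 1 point list: 2 masseter + 1 left temporal + 1 right temporal + 1 left trapezius + 1 right trapezius = 6 points, which equals the count in Table 1.

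**Step 1: reproduce the plan's own figures.** Energy = power × time.

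- Per point: 0.1 W × 60 s = 6 J (stated: 6 J).
- Fluence: 6 J / 0.0984 cm² = 60.98 J/cm² (stated: 61).
- Time per session: 6 × 60 s = 360 s = 6 minutes (stated in the schedule sentence: 6 minutes on average).
- Per session: 6 × 6 J = 36 J.
- Total: 36 J × 4 = 144 J (stated: 144 J).

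The point list, seconds, joules, fluence, 6-minute duration and tabulated total all agree.

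**Step 2: put in the 4-minute sentence.** 4 minutes = 240 s.

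- Per session: 0.1 W × 240 s = 24 J.
- Total: 24 J × 4 = 96 J.
- Ratio to Table 1: 96 / 144 = 0.667, a shortfall of one third.

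**Step 3: what keeping to 4 minutes would require.**

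- At 60 s per point: 240 / 60 = 4 points, so two listed points are left out.
- With all six points treated for equal times: 240 / 6 = 40 s per point, which is 4 J and 4 / 0.0984 = 40.7 J/cm², against the stated 60 s, 6 J and 61 J/cm².

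**Step 4: look for a reading under which both times hold.**

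- *Session length versus laser-on time.* The laser-on time alone is 6 minutes, so it does not fit into a 4-minute application time.
- *Both sides treated at once.* This is not described. Treating the six points in pairs would take 3 minutes, not 4.
- *Higher power.* 36 J in 240 s needs 36 / 240 = 0.15 W = 150 mW, against the stated 100 mW.

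None of these makes the 4-minute sentence agree with the rest.

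**The case against.** The strongest reply is that the operative instruction is per point: 60 s and 6 J, at six named sites, in both the text and the table. The 4-minute sentence is a summary. It names no point to omit and no shorter time, and every other stated parameter disagrees with it, so it looks more like a stray total than a second regimen. This stands as a comment on likelihood: the documents do not show that 96 J would in fact be delivered. It does not remove the contradiction, since that sentence alone is labelled as the total application time and it ends the operating paragraph.

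Some stronger readings are tempting but are not supported.

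- *Eight points.* The masseter points carry no side, while the others do. A reader might take them as two per side, giving 8 points, 8 minutes, 48 J per session and 192 J in total. Table 1 fixes 6 points and 144 J, and the 6-minute sentence agrees with it. What remains open is where the two masseter points lie, not how many there are.
- *Damage to the dosimetry model.* A reader might infer that the conflict feeds into the simulation. The Monte Carlo simulation section builds the model from layer thicknesses, optical properties, blood content, oxygen saturation and tissue fractions; it does not list session time or cumulative energy as an input. Validation compares simulated with measured transmittance, a fraction of incident light that does not depend on session minutes.
- *A distorted local-to-vascular energy contrast.* The ratio of total energies is not a quantity the article says it will analyse, and those arms also differ in wavelength and site.
- *An active-versus-sham imbalance.* Group 3 copies Group 1, so one consistently applied time would affect both equally. An imbalance would arise only if operators followed different sentences in the two arms, and nothing in the article says that they would.

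**Conclusion.** The article contradicts itself on the duration of the local session. The size is 4 against 6 minutes, 24 against 36 J per session, and 96 against 144 J over the course: two thirds of the tabulated energy. The two-thirds figure assumes that power stays at the stated 100 mW and that all 4 sessions are given.

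The consequence is limited to the exposure in the local arm, the sham duration in Group 3, and hence the clinical pain comparison. That the other figures agree with one another shows which sentence does not fit arithmetically. It does not show which exposure is clinically right, and that is not judged here.

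**What to change.** Reconcile the 4-minute sentence with the 6-minute sentence, the point list and Table 1, so that points × seconds × power gives the stated session time and the stated total energy. Carry the reconciled duration to Group 3. In the same correction, state the side of each of the two masseter points; this settles placement and changes neither time nor energy.

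The cost is a wording correction in one subsection, with a matching check of Table 1 and the Group 3 text. The design, sample size and planned measurements do not change.

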#### Group 2 –Vascular photobiomodulation

Vascular Photobiomodulation [VBMP] will be applied using the same device, with an infra-red wavelength of 808 nm and 100 mW, directing the light beam to the radial artery region for 10 minutes per session.

The participant will be seated in a comfortable chair with lateral support for resting their arms during the application. At the time of application, only the participant receiving the treatment, the researcher responsible for the treatment, and the guardian will be present. Everyone will wear specific goggles for eye protection. The active part of the bracelet will be covered with disposable transparent plastic [PVC] to prevent cross-contamination, and for hygiene reasons, the area to be irradiated will be pre-cleaned with a 0.2% Chlorhexidine solution. During the applications, the participant will remain seated, with the Frankfurt plane parallel to the ground. A new treatment method will be administered for 2 weeks, totaling 4 sessions [2 sessions per week] with an average duration of 10 minutes per session.

#### Group 3 –Placebo local photobiomodulation

Group 3 will undergo the same procedures described for Group 1, but the equipment will emit only the sound signal, exactly like the equipment used in Group 1, without the emission of laser light.

#### Group 4 –Placebo vascular photobiomodulation

Group 4 will undergo the same procedures described for Group 2, but the equipment will emit only the sound signal, exactly like the equipment used in Group 1, without the emission of laser light.

The dosimetric parameters for the treatments in Groups 1 and 2 are presented in Table 1. The SPIRIT schedule of enrollment, interventions, and assessments are presented in Fig 1.

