### Randomization

The participants will be informed that they will be randomly assigned to one of the four study groups that will be compared. To allocate the participants to the groups, a stratification process will be carried out based on the answers to the questionnaires and the presence of orofacial pain symptoms and the presence of headache symptoms will be considered strata. Stratification will be carried out to balance the allocation of participants in each group according to stratum.

After stratification, participants will be randomized in a 1:1:1:1 ratio into the 4 groups. The randomization list will be generated by an independent researcher in random blocks of four, electronically via the ramdomizer.org website and kept in opaque envelopes. The allocation will only be revealed to the operating researcher at the time of the intervention. A study team member, separate from the researcher who will administer the intervention, will follow the random allocation sequence to assign participants to a study group and prepare study equipment and materials. Eligible participants will be randomly assigned to Group 1—Local Photobiomodulation, Group 2—Vascular Photobiomodulation, Group 3—Placebo Local Photobiomodulation, or Group 4—Placebo Vascular Photobiomodulation using stratified block randomization generated by the study statistician.

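### Masking of the pain outcome is weak: the operator is told the allocation, the red local sham is matched on sound only, and the vascular sham is referred to the wrong arm

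*Protocol article*

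**What the plan says.** All references are to the protocol article.

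- **Operator.** The Randomization section discloses the allocation to the operating researcher when treatment is given. It also provides for another person: "A study team member, separate from the researcher who will administer the intervention, will follow the random allocation sequence". That person readies the equipment as well.
- **Who is in the room.** In the Group 2 section, "only the participant receiving the treatment, the researcher responsible for the treatment, and the guardian will be present". The Group 1 section says the same.
- **Local pair.** Group 1 is treated "with a red wavelength of 660 nm and power of 100 mW". For its sham, Group 3, "the equipment will emit only the sound signal, exactly like the equipment used in Group 1, without the emission of laser light".
- **Vascular pair.** Group 2 treatment "will be applied using the same device, with an infra-red wavelength of 808 nm and 100 mW", and the same section then speaks of a bracelet. Its sham, Group 4, has the procedures "described for Group 2, but the equipment will emit only the sound signal, exactly like the equipment used in Group 1".
- **Eyewear.** Everyone wears goggles. Their stated purpose is eye protection.
- **Power meter.** Under Light transmission, a sensor sits inside the cheek while the laser is applied over the masseter.
- **Outcome.** Under Study variables, orofacial pain is primary, and questionnaires supply the symptom information. The Sample section gives an age range of 7 to 19 years.

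**The concern.** A reported pain outcome is open to expectation. If the participant, the guardian or the person treating them knows or guesses which device is active, reported pain can shift in favour of the active arm without any effect of light. The Discussion rests the rigour of the trial on its placebo controls, so the shams must be hard to tell from their active arms.

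As described, there are three routes by which allocation can become known: an operator who has been told it, visible red light that is present in Group 1 and absent in Group 3, and a meter reading that differs between those two groups.

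The comparison between pairs is also at stake. Under Expected results, the trial is to show whether local and vascular application differ in effect. If one pair is better masked than the other, part of any such difference could be a masking artefact.

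**Working it through.** **1. What each sham is stated to match**

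| | Local pair (Groups 1 and 3) | Vascular pair (Groups 2 and 4) |
|---|---|---|
| Active light | 660 nm, red | 808 nm, infra-red |
| Exposure (Table 1) | 60 s per point, 6 points | 600 s |
| Sham sound likened to | Group 1, its own active arm | Group 1, not its own active arm |
| Light in the sham | none | none |
| Visible difference from active | red light present or absent | little or none to be expected |
| Operator told the allocation | yes | yes |

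The last two rows do different work. Knowledge held by the operator affects both pairs alike. Only the light row can make the pairs unequal.

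**2. The Group 4 wording.** The sound clause is the same in the Group 3 and Group 4 sections. For Group 3 the reference to Group 1 is right. For Group 4 the expected reference is Group 2. The Group 2 section calls the device the same one, yet mentions a bracelet that is not mentioned for Group 1. The text therefore does not settle whether a sound like that of Group 1 is also the sound of Group 2.

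**3. The power meter.** Group 3 undergoes the Group 1 procedures, which include measuring energy penetration at a masseter point. With no laser emitted, the meter would show no laser transmission in Group 3. Anyone who sees the display then learns the allocation, even if the operator was never told.

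**4. What bias of a given size would do.** The article has no figure to reproduce: the 180 participants are a convenience sample.

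- Per arm: 180 / 4 = 45, from the 1:1:1:1 ratio.
- Standard error of a difference between two arms, in SD units: sqrt(2/45) = 0.211.
- Two-sided 5% test, no true effect, bias b: type I error = Φ(b/0.211 − 1.96) + Φ(−b/0.211 − 1.96).

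| Assumed bias b | Type I error |
|---|---|
| 0 | 5.0% |
| 0.10 SD | 7.6% |
| 0.15 SD | 11.0% |
| 0.20 SD | 15.8% |

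A bias of 0.15 SD would arise, for example, if half of a pair identified the allocation and this shifted the reported pain difference by 0.3 SD (0.5 × 0.3 = 0.15). Both inputs are assumptions, as is the 5% level. If only one pair carried the bias, all of b would pass into the difference between the two sham-adjusted effects (b − 0 = b).

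**The case against.** The strongest replies are these.

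- **The vascular sham may be right in practice.** A reader might infer from the Group 4 section that the vascular sham imitates the wrong device. The documents do not support that. Group 4 first takes over the Group 2 procedures, only the sound clause names Group 1, and Group 2 is said to use the same device. The clause repeats the Group 3 wording, so a copying slip is likely. This stands: it is a cross-reference to reconcile, not proof of a mismatched sham.
- **Unequal masking is not shown.** The laser is applied in contact and everyone wears goggles, whose properties are not given. In a parallel-group trial a Group 3 participant has no active session to compare with. This stands in part: the wavelengths make inequality plausible, but it depends on whether the red light can be seen.
- **The operator may not collect the pain data.** The article does not say who administers the questionnaires. So the operator's knowledge does not show that the pain assessor is unblinded. That stands. It does not remove the exposure of the participant and guardian to an informed operator during treatment.
- **The article is condensed.** Detail on who is blinded may be in fuller documents, so its absence is not held against the plan. The disclosure to the operator and the sound-only sham, however, are stated choices.
- **The bias sizes are invented.** They are assumptions and cannot set the severity of the point.

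**Conclusion.** The point holds in a limited form. As written, the plan tells the operator the allocation and gives the red local arm a sham matched on sound alone, for a primary outcome of pain with questionnaire symptom data. That is weak masking, and much of it is avoidable with staff already in the plan. The meter reading adds a further cue in the local pair.

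Two parts are conditional. Masking is weaker in the local pair than in the vascular pair only if red light is visible past the goggles and the contact tip. The Group 4 reference to Group 1 is a contradiction to clear up against the Group 2 section, with its single device and its bracelet.

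The size of any bias is unknown. The type I error figures of about 11% at 0.15 SD and 16% at 0.20 SD show the sensitivity of a 45-per-arm comparison to assumed bias. They do not estimate what will happen in this trial.

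**What to change.** 1. Have the separate team member under Randomization preset the device to active or sham, and tell the operator only the site to treat.
2. Keep the power-meter display out of view of the operator, participant and guardian. Someone else should record the reading.
3. Use eyewear that keeps the stated laser protection and also hides the red light from the participant and guardian.
4. Have the pain questionnaires completed without input from anyone who knows the allocation.
5. Record each participant's guess of allocation at the end, by group.
6. Correct the Group 4 sentence, and reconcile it with the single device and the bracelet in the Group 2 section, so that each sham is stated to match its own active arm.

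**Cost.** Items 1 and 4 need a change of procedure, item 5 one question, and item 6 wording. Item 2 needs a second person or a shielded display. Item 3 needs eyewear checked for both protection and masking. No visits or participants are added. The remaining weakness is that the operator may still see the red light in the local pair, so operator masking there stays partial and should be reported as such.

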**Fig 1 pone.0309073.g001:**
[figure not shown]
The SPIRIT schedule of enrolment, interventions, and assessments.

**Table 1 pone.0309073.t001:** Dosimetric parameters for photobiomodulation application.

PARAMETERS	RED LASER [Local]	INFRARED LASER [Transcutaneous Systemic]
Wavelength [nm]	660	808
Mode	Contínuo	Contínuo
Power [mW]	100	100
Aperture Diameter [cm]	0,354 [beam diameter with spacer]	0,354 cm
Beam Area [cm^2^]	0,0984 [with spacer]	0,0984 cm^2^
Exposure Time [s]	60 per point	600 s
Fluence [J/cm^2^]	61	-
Energy [J]	6 per point	60 J
Number of irradiated points	6	Systemic
Application Technique	Contact	Contact
Number of sessions	4	4
Treatment Frequency	2 times per week	2 times per week
Total Irradiated Energy [J]	144 J	240 J

#### Laser safety measures

The appointments will take place in a dental office, which will have its door closed, preventing people from entering during the use of the laser. Everyone will wear specific glasses for eye protection.

#### Monte Carlo simulation

The Monte Carlo technique will be employed to simulate the fluence profile, energy deposited in different tissue layers of the cheek and index finger, and transmittance, using light of wavelengths 660 nm and 808 nm. In an initial phase, a Monte Carlo model will be developed, considering the morphological structure of the tissues to be treated, approximating their structure to a planar and laminar model consisting of four layers: epidermis, dermis, subcutaneous fat, and muscle [15].

The thicknesses of each layer will be obtained from the literature, and their values will be varied in predefined intervals consistent with literature findings for different age groups and BMI values. The optical properties of each layer, including absorption and scattering coefficients, anisotropy coefficient, and refractive index, will be gathered from bibliographic research, considering the expected variability for the sample under study.

A model for the absorption coefficient will be used, accounting for blood content in each layer, blood oxygen saturation level, as well as fractions of fat, melanin, and water in each tissue layer. Based on the preliminary study, a database will be established aiming to establish a relationship between energy deposited in tissues and different anthropometric characteristics [13, 16].

Special attention will be given to the relationship between energy deposited in the epidermis and muscle, to establish a compromise between safety limits and treatment effectiveness. Simulated transmittance values will be subsequently compared with values measured in volunteers, considering measurements of tissue thickness by ultrasound, skin type, BMI, and blood saturation levels. A computational implementation of the tissue optical model and the Monte Carlo simulation model will be developed based on Marti et al.’s MCMatlab code, available online [https://github.com/ankrh/MCmatlab], using Matlab® software, version 2022.

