Therefore, the aim of this project is to evaluate a Monte Carlo simulation model to predict the distribution of energy and its effects related to anthropometric and hemodynamic variables in photobiomodulation treatment with both local and systemic applications across different age groups [13].

With the development of this study, we expect to create and validate a Monte Carlo Simulation model to calculate the appropriate dosimetry for photobiomodulation therapies in orofacial pain control, according to the physical and physiopathological characteristics of each person. In this way, healthcare professionals can deliver energy closest to the ideal in treatment, achieving desired results, reducing unnecessary exposure time, and avoiding under or over-treatment.

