#### Light transmission

The SPER Scientific Pocket Laser Power Meter device [Scottsdale, AZ, USA] will be used. Light transmission will be assessed through the index finger and cheek [masseter] of each participant. The sensor of the equipment will be positioned on the inner region of the cheek at the same time the researcher is applying the laser on the masseter region [2 points].

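### The model is to be validated for systemic as well as local application, but the radial artery site has no simulated or measured light data, and the stated tissue stack does not span the paths measured

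*Protocol article*

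**What the plan says.** The Introduction sets the aim as a simulation model that predicts energy distribution and its effects "in photobiomodulation treatment with both local and systemic applications". The Abstract (Methods) claims the same two modes and says that in vivo and simulated transmittance will be compared in order to validate the model.

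Under Monte Carlo simulation, the model is to be built "considering the morphological structure of the tissues to be treated", approximated as a "planar and laminar model consisting of four layers: epidermis, dermis, subcutaneous fat, and muscle". The quantities simulated are the fluence profile and the "energy deposited in different tissue layers of the cheek and index finger, and transmittance, using light of wavelengths 660 nm and 808 nm". Simulated transmittance is then compared with values measured in volunteers, taking account of ultrasound thickness, skin type, BMI and blood saturation.

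Under Light transmission, readings are taken through the index finger and the cheek. For the cheek, "The sensor of the equipment will be positioned on the inner region of the cheek" while the laser is applied over the masseter. The section on fat and muscle thickness describes ultrasound over the masseter only. Group 2 is treated by "directing the light beam to the radial artery region for 10 minutes per session", with a bracelet.

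**The concern.** Validation is defined as agreement between simulated and measured transmittance, so it can hold only where both exist and describe the same light path. Two gaps follow.

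First, the systemic site appears in neither half of the comparison. Followed as written, the study could report a dosimetry model validated for systemic application with no light data from the place where systemic treatment is given.

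Second, the stated layers end at muscle, whereas the readings are taken beyond it: inside the mouth for the cheek, and on the far side of the digit for the finger. A disagreement could then come from missing tissue and be read as patient variability, and an agreement could be accidental. The same model is meant to inform the balance between energy in the epidermis and energy in muscle, so an unrecognised geometric error would carry into the dosimetry that the study intends to deliver.

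**Working it through.** **1. Reproduce the plan's energy figures (Table 1).**
- Local: 0.1 W × 60 s = 6 J per point; 6 / 0.0984 = 61 J/cm²; 6 J × 6 points × 4 sessions = 144 J.
- Vascular: 0.1 W × 600 s = 60 J per session; × 4 sessions = 240 J.

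These agree with the table.

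**2. Set the sites side by side.** Sources: Group 1, Group 2, Light transmission, Thickness of the fat and muscle layer, Monte Carlo simulation.

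| Site | Irradiated in an active arm | Simulated | Transmission measured | Ultrasound thickness |
|---|---|---|---|---|
| Cheek over masseter | Yes, 2 of 6 local points | Yes | Yes, sensor inside cheek | Yes |
| Temporal and trapezius | Yes, 4 of 6 local points | No | No | No |
| Radial artery region | Yes, vascular arm | No | No | No |
| Index finger | No | Yes | Yes | No |

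**3. Express coverage as energy.**
- Local arm: the cheek accounts for 2 × 6 J × 4 = 48 J of 144 J, or 33%.
- Vascular arm: the simulated and measured sites account for 0 J of 240 J.

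**4. Compare the stated layers with the measured paths.** That mucosa, bone and exit-side skin lie in these paths is general anatomy, not a statement in the protocol.
- Cheek: the stack is epidermis, dermis, fat, muscle. Light reaching an intra-oral sensor also crosses oral mucosa.
- Finger: light passing through the digit crosses skin, fat, bone or tendon, then fat and skin again, with little or no muscle. If the stated stack is used, it lacks the far-side tissue and bone but contains muscle that is hardly there.

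**5. What can be said about size.** The protocol gives neither attenuation coefficients nor layer thicknesses, so what follows is illustration only. Leaving out a layer of thickness d multiplies true transmittance by exp(−μd) relative to the simulated value. Assume μ of 1 to 5 per cm and d of 1 to 3 mm for the cheek:
- exp(−1 × 0.1) = 0.90
- exp(−5 × 0.3) = 0.22

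The possible effect thus runs from small to large, depending wholly on the assumed values. For the finger, omitted bone and far-side tissue push simulated transmittance up and surplus muscle pushes it down. The net error has no known sign, and no factor is given here.

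**The case against.** The strongest reply is that the cheek over the masseter is treated, measured, scanned and simulated. That is true, and a reader who infers that the geometry is mismatched throughout would be wrong: at the cheek the only gap is the exit layer. If the inner edge of the muscle layer is meant to sit at the inner surface of the cheek, mucosa is already lumped in and the error is smaller.

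The article also presents the stack as an approximation for an initial phase and does not say which stack the finger uses. Site-specific layer tables may stand in a fuller document, so use of the four layers for the finger is an inference. It is a reasonable one: no other structure is named, and the next step described is the comparison with volunteers.

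A reader might go on to infer that misfit will be tuned away through the optical properties. The protocol describes no fitting step; those properties are to come from the literature.

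A reader might also infer that nothing at all can be learned about systemic application. That goes too far. Pain, oxygen saturation, blood pressure, heart rate, lactate and haemoglobin are collected, and their relation to patient characteristics does not need transmittance at the radial site. The simulation also runs at 808 nm, the vascular-arm wavelength, with blood content and saturation in the absorption model.

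None of this supplies simulated or measured light data at the radial site, or makes a stack ending at muscle describe an intra-oral reading.

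**Conclusion.** The concern holds in a limited form.

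- **Systemic site.** This rests on the text alone. The aim covers systemic application, but the radial artery region is not simulated, has no transmission reading and has no thickness measurement. Simulated light delivery there cannot be validated by the stated comparison: 0 of 240 J falls on a site with data.
- **Measured paths.** As stated, the stack lacks an exit layer for the cheek reading, and lacks bone and far-side tissue for the finger reading. This rests on general anatomy and, for the finger, on the inference that the one stated stack applies. If the mucosa is simply left out, simulated cheek transmittance is too high by an amount that the protocol does not allow one to calculate. For the finger, both size and direction are unknown.

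The point concerns the scope of the validation claim and the like-for-like basis of the comparison. It does not bear on the randomised comparison of pain, nor does it show that the cheek model will fail.

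**What to change.** 1. Limit the validation aim and conclusion, in the Abstract, Introduction and Expected results, to local application at the cheek (masseter). This also deals with the temporal and trapezius points, which likewise have no light data.
2. Describe any simulation of the radial site as exploratory and unvalidated. Simulation alone would not close the gap, because no transmission or thickness is measured there.
3. Add an oral mucosa layer to the cheek stack, or state that the muscle layer is drawn to the inner surface and includes it.
4. Give the finger its own stack (skin, fat, bone/tendon, fat, skin), or drop the finger from the validation comparison. No finger thickness is measured, so its layers would rest on literature values; say so.

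The cost is a little more simulation work in code already chosen and a narrower stated claim. No treatment or visit changes.
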